## Abstract

**Background:**

Vitamin D deficiency is associated with multiple adverse health outcomes including increased morbidity and mortality in the general population and in critically ill patients. However, no randomized controlled trial has evaluated so far whether treatment with sufficiently large doses of vitamin D can improve clinical outcome of patients in an intensive care setting.

**Methods/design:**

The VITdAL@ICU trial is an investigator-initiated, non-commercial, double-blind, placebo-controlled randomized clinical trial. This study compares high-dose oral cholecalciferol (vitamin D3) versus placebo treatment in a mixed population of 480 critically ill patients with low 25-hydroxyvitamin-D levels at study enrollment (≤ 20ng/ml). Following an initial loading dose of 540,000 IU of vitamin D3, patients receive 90,000 IU of vitamin D3 on a monthly basis for 5 months. The study is designed to compare clinical outcome in the two study arms with the primary endpoint being length of hospital stay. Secondary endpoints include among others length of ICU stay, the percentage of patients with 25(OH)D levels > 30 ng/ml at day 7, ICU and hospital mortality and duration of mechanical ventilation. We describe here the VITdAL@ICU study protocol for the primary report.

**Discussion:**

This trial is designed to evaluate whether high-dose vitamin D3 is able to improve morbidity and mortality in a mixed population of adult critically ill patients and correct vitamin D deficiency safely.

**Trial registration:**

ClinicalTrials: NCT01130181

## Background

Vitamin D is a key regulator in calcium and phosphorus metabolism and likely confers physiologically relevant pleiotropic functions that include cardioprotective and immunomodulatory effects as well as improvement of antimicrobial action
[1-6]. Profound vitamin D deficiency in humans causes rickets in children or osteomalacia in adults together with vitamin D myopathy, whereas low vitamin D levels may be associated with an increased prevalence of a multitude of other diseases
[1,6] including an increase in mortality
[7,8].

Moreover, a systematic review concluded that intervention with cholecalciferol significantly reduced mortality in predominantly elderly, institutionalized women
[9]. To date, only few large interventional randomized trials have investigated the effect of vitamin D on clinical outcomes. The rationale for pleiotropic effects of this substance is based on the fact that the vitamin D receptor (VDR) is almost ubiquitously expressed, and the vast majority of cells respond to 1,25(OH)2D exposure. Hundreds of genes with vitamin D receptor response elements directly or indirectly influence cell cycling, cell proliferation, differentiation and apoptosis
[6,10].

### Vitamin D in ICU patients

Endogenous synthesis in the presence of UV-B radiation is the main source of vitamin D. Therefore, immobilized and elderly individuals are prone to develop vitamin D deficiency. Low vitamin D levels are highly prevalent in critically ill adults and children
[11-18]. Unfortunately, no uniform definition of vitamin D deficiency exists and tissue levels of the major active metabolite 1,25(OH)2D are currently not measurable. Today most guidelines agree, however, that a “low” vitamin D status is present when serum 25(OH)D levels are below 20 ng/ml
[1,19]. Special concerns in the ICU setting relate to the issue as to whether the definition of vitamin D deficiency should be the same as in the general population or whether special metabolites of vitamin D should be considered in this definition as well
[20]. Insufficient vitamin D levels could affect this population in various ways
[21]. Over the last years, several groups have reported on an inverse association between vitamin D levels in critically ill patients and severity of disease including length of ICU stay and mortality
[13,14,16,22,23]. Moreover, vitamin D levels decline further during ICU stay
[24] which is explained by insufficient replacement of vitamin D via enteral or parenteral nutrition in the absence of UV-B exposure. To date, only few and small intervention studies (n=22-33 patients) that were not designed to demonstrate effects on clinical outcomes have been published
[12,25-27].

### Vitamin D and proposed clinical effects pertinent to the critically ill patient

#### Calcium homeostasis and bone turnover

In critically ill patients, hypocalcemia is frequently present and has been related to increased morbidity and mortality
[28-30]. Reasons for hypocalcemia are not well understood, but besides elevated levels of IL-6, vitamin D deficiency may play a decisive role
[31-34]. Without correction of vitamin D deficiency, calcium levels may be impossible to normalize
[29]. To maintain serum calcium levels, parathyroid hormone levels rise and induce accelerated bone resorption which is aggravated by prolonged immobilization ultimately resulting in significant bone loss. Interestingly, even relatively low doses of intravenous vitamin D (500 IU daily) might be able to attenuate this detrimental physiological response
[12].

#### Cardiovascular system

The heart is an important target organ for vitamin D, both on a genomic and nongenomic level
[35]. Cardiomyocytes express the VDR. Severe hypocalcemia may cause life-threatening, reversible heart failure
[36]. Vitamin D seems to inhibit activation of the renin-angiotensin system as well as the expression of genes involved in the development of myocardial hypertrophy
[37]. There is accumulating evidence that vitamin D deficiency may be an important factor in the development of congestive heart failure and sudden cardiac death
[38]. In chronic hemodialysis patients, calcitriol supplementation is associated with reduction of cardiac hypertrophy and a reduction of QT dispersion
[39], the latter being considered a major risk factor for arrhythmia and sudden cardiac death.

Our group found a negative correlation of 25(OH)D with NT-pro-BNP levels, NYHA functional classes and impaired left ventricular function
[38]. Hazard ratios for death attributable to heart failure and sudden cardiac death were 2.8 and 5.0, respectively, when patients with severe vitamin D deficiency (25(OH)D <10 ng/ml) were compared with those considered having optimal serum levels (25(OH)D >30 ng/ml)
[38]. The anti-inflammatory properties of vitamin D may play an additional role in congestive heart failure
[40]. In animal models, vitamin D deficiency is associated with myocardial hypertrophy and fibrosis leading to aberrant cardiac contractility and relaxation
[41,42]. Moreover, calcitriol treatment was able to prevent cardiac hypertrophy under in-vitro conditions or in VDR knock-out animals
[41,42].

#### Immune system/sepsis/inflammation

Vitamin D acts on both the adaptive and innate immunity systems. Most cells of the immune system express the VDR
[6]. It enables macrophages to respond to and kill bacterial and viral organisms. In line with this is the observation of impaired macrophage function in VDR knock-out mice
[6]. Vitamin D also exerts an influence on epidermal keratinocytes to fulfill their barrier function
[43]. Monocytes cultured in severely vitamin D-deficient plasma express less cathelicidines and improve their function with 25(OH)D as well as 1,25(OH)2D
[44]. Cathelicidines are important antimicrobial peptides that are of great interest in critically ill patients because they constitute part of the initial defense line against pathogens. They are expressed in epithelia of airways, the bladder and gastrointestinal tract, which are all considered important entry sites of nosocomial infections. Treatment of normal human bronchial epithelial cells with 1,25(OH)2D results in a 10-fold up-regulation of cathelicidin mRNA levels after 12 hours
[45]. In septic ICU patients, a positive correlation between circulating 25(OH)D and LL-37 levels, the active fragment of cathelicidin, has been reported
[46]. In a large retrospective study, the risk for blood culture positivity was significantly higher in vitamin D deficient critically ill patients
[13]. Of interest in this context is also the finding that sepsis incidence and case-fatality rates are significantly higher in winter despite similarities in disease severity during summer time
[47].

#### Muscle

Severe vitamin D deficiency is associated with myopathy, decreased muscle strength and an increased risk for falls
[1]. In intensive care, this may translate to the necessity of prolonged mechanical ventilation and difficulties during remobilization and weaning from ventilatory support in patients with low vitamin D status. In randomized controlled trials, vitamin D supplementation improved muscle strength in elderly patients
[48] and decreased the frequency of falls
[48-50].

### Guidelines and practices

For the general population, the Institute of Medicine (IOM) recommends a daily allowance for adults of 600 to 800 IU
[51], while the Endocrine Society Guideline recommends 1,500–2,000 IU of vitamin D3 per day for the at-risk population
[52]. Upper daily limits for adults are 4,000 (IOM)–10,000 (Endocrine Society) IU per day. Guidelines for parenteral nutrition recommend 200 IU per day and typical enteral nutrition formulas contain 200–300 IU of ergocalciferol or cholecalciferol per 1000 ml. Available over the counter multivitamin preparations commonly contain 200 IU of vitamin D2 or D3. Currently, there is no intravenous vitamin D-monopreparation available, although high-dose intramuscular preparations may be an option in selected patients.

### Rationale of the study and hypothesis

In summary, vitamin D plays a pivotal role in calcium homeostasis and is, based on current knowledge, associated with disease severity and mortality in critically ill patients. Moreover, vitamin D exhibits a number of pleiotropic effects that are of special interest to the ICU patient
[20,53,54] However, so far it is unclear whether a low vitamin D status is causally linked to adverse outcomes or merely an epiphenomenon reflecting poor health status. In contrast to previous clinical trials that failed to show a benefit for correcting hormonal insufficiencies in critical illness (e.g. administration of growth hormone or steroids)
[55,56], one has to bear in mind that vitamin D not only acts on endocrine, but also autocrine level which allows for tissue-specific control of 1,25(OH)2D regulation and action that may be completely independent of circulating calcitriol levels. As far as we know now vitamin D also has an excellent safety profile with a broad therapeutic window
[19,57].

The hypothesis of this first large RCT is that supplementation with a sufficiently large dose of vitamin D leads to a fast correction of low vitamin D status and possibly to clinical benefits, particularly relating to immune, cardiac and muscle function. Because these potential benefits likely occur at various functional hierarchies, we chose “length of hospital stay” as a primary surrogate marker for a change in morbidity in this patient group.

### Results from the pilot study relevant for the design of this trial

To optimize study design and ascertain safety and efficacy of the chosen loading dose of 540,000 IU of cholecalciferol, we performed a pilot trial in 25 medical critically ill patients with vitamin D deficiency
[25]. Adverse effects like hypercalcemia or hypercalciuria did not occur in this pilot study and vitamin D levels increased significantly in most patients within two days, although 2 out of 10 patients showed no or only a modest rise in 25(OH)D levels at day 7. We therefore chose to continue with the same loading dose, but added monthly maintenance doses of vitamin D to the study protocol.

### Justification of high-dose vitamin D3 intervention

The half-life of 25(OH)D following oral cholecalciferol supplementation allows the administration of large doses. In elderly patients with vitamin D deficiency and healthy individuals, large loading doses rapidly and safely normalized 25(OH)D levels
[58-60]. However, an annual high-dose intervention was associated with a higher risk of falls and fractures in elderly patients
[61]. Some contraindications such as sarcoidosis and other granulomatous diseases also need to be considered before administration of a high loading dose
[62,63]. Following publication of the detrimental effects of a high-dose vitamin D intervention on the risk of falls and fractures
[61], we decided to nevertheless proceed with the initial study protocol because in our population, a rapid restoration of vitamin D status may still have positive effects on patient immunity and even muscular function. We are aware that smaller doses of vitamin D3 are likely an effective treatment option for most patients with low vitamin D status within months but this time span may be too long during critical illness.

## Methods/design

### Study design

The VITdAL@ICU trial is an investigator-initiated, non-commercial, double-blind, placebo-controlled randomized clinical trial. This study compares high-dose oral cholecalciferol (vitamin D3) versus placebo treatment in a mixed population of 480 critically ill patients with low 25(OH)D levels at study enrollment (≤ 20ng/ml). Following an initial loading dose of 540,000 IU of vitamin D3, patients receive 90,000 IU of vitamin D3 on a monthly basis for 5 months resulting in a total treatment/observation period of 6 months. The VITdAL@ICU study is conducted at the Medical University of Graz, Austria, a tertiary care university hospital with a catchment area covering the Southeast of Austria (population approximately 1.5 million). It recruits patients from five ICUs: medical (15 beds), neurological (8 beds), cardiothoracic surgery (13 beds) and two mixed surgery units (12 and 10 beds, respectively).

### Eligibility criteria for inclusion and recruitment

Upon admission to one of the five participating ICUs, all adult patients undergo screening for study participation. Patients ≥18 years who are expected to stay at the ICU ≥48 hours and are vitamin D deficient (25(OH)D level ≤ 20 ng/ml) are screened for inclusion and exclusion criteria. The following patients are not considered eligible for inclusion: patients expected to die within the upcoming 24 hours, with severely impaired gastrointestinal motility (ileus, gastric volume > 400 ml), contraindication for study drug application (orally or via feeding tube), readmission after participation in the VITdAL@ICU pilot study, enrolment in another intervention trial or documented hypercalcemia (total calcium >2.65 or ionized serum calcium >1.35 mmol/l). Patients with a history of granulomatous disease (tuberculosis, sarcoidosis), recent kidney stones (≤ 1 year) as well as pregnant or lactating women are also excluded from this trial. An overview of the study procedures is given in Figure
1.

**Figure 1 F1:**
[figure not shown]
Trial procedures flow sheet.

### Ethical aspects and informed consent

The institutional ethical committee of the Medical University of Graz, Austria (reference number 21–214 ex 09/10, EudraCT-Nr.: 2010-018798-39), and the Austrian Agency for Health and Food Safety (AGES) approved the study. Informed consent is obtained prior to inclusion into the study according to the Austrian law. The patient can withdraw from the study at any time, without giving any reason and without impact on treatment. A register is kept of all patients evaluated for inclusion and of patients who choose to withdraw from the study.

### Randomization

Patients at each of the five ICUs are randomly assigned to one of the two treatment study groups, “Vitamin D” or “Placebo”, in a 1:1 ratio, using the web-based randomization tool “Randomizer for Clinical Trials” (
http://www.randomizer.at). Block randomization is used with patients stratified according to ICU and gender.

### Study drug preparation, labeling and intake

The cholecalciferol preparation is provided by Fresenius Kabi, Austria. As placebo, oleum arachidis is used. Identical bottles of study medication containing 180,000 IU of cholecalciferol in 15 ml of oleum arachidis or corresponding placebo are prepared and labeled at the institutional pharmacy. Study medication is stored at room temperature. For usage of the study medication outside of the ICU, the patient, next of kin or continuing caregiver/s are instructed by the study team and receive oral and written information on how and when to take the remaining study medication. Furthermore, they are asked to refrain from additional use of vitamin D over the following 6 months. Additionally, the patient’s family practitioner and, if applicable, treating general ward or rehabilitation facility are personally informed or contacted by telephone and instructed about the study.

### Interventions

“Vitamin D”: Patients randomized to the “Vitamin D” group receive a loading dose of 540,000 IU of vitamin D3 orally or via feeding tube. This dose equals three bottles of a commercially available vitamin D preparation in Austria: Oleovit D3® solution; concentration of cholecalciferol is 400 IU vitamin D3/drop of oleum arachidis. Total carrier volume is 45 ml. From month 1 to 5, patients receive monthly maintenance doses of 90,000 IU cholecalciferol.

“Placebo”: Patients randomized to the “Placebo” group receive oleum arachidis in the same volume and time schedule as “Vitamin D” patients.

### Routine low-dose vitamin D supplementation in both study arms during ICU stay

Patients in both study arms are allowed to receive regular low dose (approximately 200 IU per day) vitamin D supplements via enteral and/or parenteral nutrition as deemed appropriate by the treating physicians during stay at the ICU, but are not allowed to receive any vitamin D preparations during their stay at the general ward or at home.

### Handling of readmissions to ICU

Patients who are readmitted to intensive care after participation in the VITdAL@ICU trial are not eligible for reinclusion.

### Blinding of treatment allocation

All persons involved in patient care of the RCT are blinded to treatment allocation and all study-related activities are carried out in a double-blind fashion.

### Primary outcome measures

The primary efficacy endpoint for this RCT is the length of stay (LOS) in the hospital starting from application of the study medication. The end is defined as the time of hospital discharge or death of the patient. Further admissions to rehabilitation facilities are not taken into account. Before unblinding all relevant facilities are independently classified by two study team members.

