### Sample size calculation

The sample size was calculated to detect a difference in mean length of hospital stay of 2 days with 80% power and a significance level of 5%. Using the Mann–Whitney U-Test for sample size calculation, a group size of 234 is needed to show a reduction of 2 days (equivalent to 14%) of the primary study outcome based on a mean hospital stay of 14 days and standard deviation of 7 days for the control group. To consider drop-outs of the study, a sample of 480 patients (240 per arm) was considered appropriate.

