### Statistical analyses

The primary analysis for comparing length of hospital stay between the two groups will be made using the Mann–Whitney U-test. For secondary endpoints, differences between the two groups will be evaluated with the t test or Mann–Whitney U-test for continuous variables as appropriate and for categorical variables with the chi-square or Fisher Exact test. Survival endpoints will be displayed in Kaplan-Meier plots and compared by the log rank test. Furthermore, linear and logistic regression models will be applied to adjust for age, disease severity and 25(OH)D.

A CONSORT diagram will be reported (Figure
2). Analyses will be performed both on intention to treat and per protocol population with the intention-to-treat population as the primary. To assess compliance with the study protocol, the number of study drug maintenance doses will be reported.

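### The primary endpoint ends hospital stay at discharge or death alike, so the Mann–Whitney test ranks an early in-hospital death as a good outcome and is biased if treatment changes mortality

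*Protocol article*

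**What the plan says.** Protocol article, Primary outcome measures: the endpoint is "length of stay (LOS) in the hospital starting from application of the study medication", and for the stop of the clock, "The end is defined as the time of hospital discharge or death of the patient". The two ways of ending the stay are not distinguished.

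Statistical analyses: "The primary analysis for comparing length of hospital stay between the two groups will be made using the Mann–Whitney U-test". The intention-to-treat population is primary, so in-hospital deaths stay in the comparison.

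Sample size calculation: "a group size of 234 is needed to show a reduction of 2 days (equivalent to 14%) of the primary study outcome". Success is thus a shorter stay.

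Rationale of the study and hypothesis: length of stay was chosen "as a primary surrogate marker for a change in morbidity in this patient group".

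No text ranks deaths last, censors them or treats death as a competing event for the primary endpoint. Mortality (ICU, hospital, 28-day, 6-month) appears only among the secondary and safety endpoints.

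**The concern.** A patient who dies on day 3 gets a better rank than one who goes home alive on day 10. Eligibility excludes only patients expected to die within 24 hours, so later in-hospital deaths will occur in this population. The abstract's Discussion says the trial is to evaluate whether vitamin D improves morbidity and mortality.

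If treatment saves patients who would have died early, they enter the treated arm with longer stays and count against it. If treatment causes early deaths, they shorten stay in the treated arm and count in its favour. Either way the primary conclusion would be distorted, and length of stay would no longer serve as a marker of morbidity.

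**Working it through.** **The plan's own figure.** With a difference of 2 days, SD 7, 80% power and two-sided 5% (sidedness is not stated), n per arm = 2 × (1.96 + 0.842)² × 7² / 2² = 192.3, so 193. Dividing by the Mann–Whitney efficiency gives 193/0.955 = 203, or 193/0.864 = 224 at the lower bound. Noether's formula gives 205. The stated 234 is not reproduced but errs on the large side, and 234/(1 − 0.025) = 240 fits the final size. Nothing below depends on this figure.

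**The mechanism in one formula.** Let p0 and p1 be in-hospital mortality on placebo and vitamin D. Let q be the probability that a patient who dies has a shorter recorded stay than a patient discharged alive. Suppose treatment affects mortality only. The probability that a vitamin D patient has the shorter stay, which is what Mann–Whitney tests against ½, is

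θ = ½[p1p0 + (1 − p1)(1 − p0)] + p1(1 − p0)q + p0(1 − p1)(1 − q),

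which simplifies to θ − ½ = (p1 − p0)(q − ½).

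- If mortality is equal, the shift is zero and the test keeps its size.
- If q is above ½ (deaths come early), higher mortality on vitamin D moves the test toward benefit, and lower mortality moves it the other way.
- If q is below ½ (deaths come late), the signs reverse.

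**Inputs.** From the article: 240 per arm, mean 14, SD 7, 5% level. Assumed: two-sided test; mean and SD apply to survivors, with lognormal stay; exponential time to death with mean 5 to 20 days; mortality 25% to 35%.

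**Harm only: mortality 25% to 35%, no effect in survivors.** The approximate standard error of θ is 1/√(6 × 240) = 0.0264. For a mean death time of 5 days, q = 0.889, the shift is 0.10 × 0.389 = 0.0389, and 0.0389/0.0264 ≈ 1.48. The chance of a significantly shorter stay is P(Z > 1.96 − 1.48) ≈ 31%. All rows:

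| Mean death time (days) | q | Shift in θ | False benefit, formula | False benefit, simulated |
|---|---|---|---|---|
| 5 | 0.889 | 0.0389 | 31% | 31% |
| 7 | 0.810 | 0.0310 | 22% | 20% |
| 10 | 0.704 | 0.0204 | 12% | 12% |
| 14 | 0.593 | 0.0093 | 5% | 4% |
| 20 | 0.477 | −0.0023 | 2% | 2% |

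The nominal one-directional rate is 2.5%. If mortality rises only to 30%, the shift halves. The formula then gives 11%, 9%, 6%, 4% and 2%, and other shapes of the death-time distribution give 11% to 14% at 5 days.

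**Benefit on both: 2-day reduction in survivors, mortality 35% to 25%.** Simulated power of the test as written, against the same test with deaths ranked worst:

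| Mean death time (days) | As written | Deaths ranked worst |
|---|---|---|
| 5 | 8% | about 95% |
| 7 | 16% | about 95% |
| 10 | 30% | about 95% |
| 14 | 45% | about 95% |
| 20 | 60% | about 95% |

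**Equal mortality.** With no effect on stay, simulated type I error stays near 5%. With a 2-day effect in survivors and 20% mortality in both arms, power is about 70% as written and about 61% with deaths ranked worst.

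**The case against.** Three stronger readings are tempting, and the article does not support them.

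- *The test points the wrong way for every death.* It does not. A death late in the stay ranks as a long, and so unfavourable, stay. The false-benefit signal has nearly faded at a mean death time of 14 days and is gone at 20. The article gives no time to death, so even the sign rests on an assumption.
- *The sample size ignores deaths.* The article gives the mean of 14 and SD of 7 for the control group, not for survivors. Under its own endpoint definition these may already include deaths. Treating them as survivors' figures is an assumption made here.
- *Harm would go unseen.* Mortality is reported separately, and blinded 28-day checks were planned after 100 and 240 patients. In the 25% to 35% scenario with mean death times of 5 to 10 days, a significantly shorter stay without a significant difference in hospital mortality occurs in only about 1.5% to 3.1% of trials.

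It can also be said that the large figures need a mortality effect of 10 percentage points, that worst-rank scoring turns a morbidity marker into something else, and that an analysis plan not shown may hold a sensitivity analysis.

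What stands after all this is the stated rule. The article itself fixes the endpoint, how death enters it and the test, so this is not a detail left to another document. Separate mortality endpoints let a reader see a mortality difference but do not correct the primary test. The article's Discussion leaves adequate power for mortality to future larger trials, so a real difference could distort the primary result without being significant itself.

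**Conclusion.** The concern holds in a limited form. As written, an in-hospital death that precedes typical discharges scores as a good outcome, and no other text repairs this. The primary test is biased only if treatment changes mortality; deaths that come early push it toward benefit when mortality rises and toward no effect when it falls. Under the assumptions above, false benefit runs from about 31% down to the nominal level as mean death time goes from 5 to 20 days. Power against a true joint benefit runs from about 8% to 60%, where ranking deaths worst gives about 95%. These sizes rest on assumed mortality and death times and on applying the plan's mean and SD to survivors. They illustrate the risk and do not forecast this trial's result.

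**What to change.** Before unblinding, define the primary outcome as time to hospital discharge alive, with in-hospital death never counted as discharge. Either give deaths the worst rank in the same Mann–Whitney test, or treat death as a competing event and use Gray's test. If the present endpoint is kept, prespecify one of these as a key sensitivity analysis that must agree before benefit is claimed. In both cases report hospital mortality and stay among survivors beside the result, and restate power under a stated control mortality.

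No new data are needed: the endpoint already requires the date of discharge or death, and vital status is recorded. The cost is still more than wording:

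- The primary endpoint becomes partly a mortality composite.
- Power falls when mortality is equal (about 70% to 61% at 20% mortality).
- The Discussion reports that 28-day mortality was already compared between the groups, in blinded form, after 100 and 240 patients. The change should therefore be dated and documented as made without access to unblinded data.
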